### Mediation and moderation analyses

Week-to-week changes in facets of emotion regulation will be tested as mediators of POET effects on mental health symptoms, using parallel process latent growth curve modeling with a competing mediator (SEQ). Candidate moderators such as baseline emotion regulation, symptoms of depression and anxiety (RCADS-47), clinical global symptom severity (CGI-S), NSSI occurrence, global functioning (C-GAS), age, and parental coping (CCNES-A) will be assessed before randomization and investigated as moderators and predictors of treatment outcome (i.e., improvement in symptom severity). Moderated treatment effects will be examined using CLMM that include interaction terms between POET and the candidate moderators.

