### Secondary objective(s)

Secondary objectives include examining durability of treatment effects on clinical global symptom severity, and treatment effects on emotion regulation, mental health symptoms and, functioning as well as conducting a health economic evaluation.

Additional secondary aims include a mediation analysis to test whether improvements in emotion regulation mediate treatment effects, moderation analyses, and assessments of the durability of treatment effects and other distal outcomes.

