## Research questions and hypotheses

1. What are the effects of POET on mental health problems (clinical global symptom severity, mental health symptoms and functioning)?

Hypothesis 1.1: Compared to the active control condition, POET will result in greater reductions in clinical global symptom severity and mental health symptoms, and improvement in functioning immediately after treatment (primary endpoint) and 3-months after treatment.

1. What are the effects of POET on emotion regulation?

Hypothesis 2.1: Compared to the active control condition, POET will result in improved emotion regulation (i.e., reduced maladaptive and enhanced adaptive emotion regulation immediately after treatment and 3-months after treatment.

1. Are reductions in mental health problems during POET treatment mediated through emotion regulation?

Hypothesis 3.1: It is hypothesized that improvement in emotion regulation will temporally precede and mediate reductions in mental health problems during treatment.

1. Is POET cost-effective

Hypothesis 4.1: It is hypothesized that POET will be cost-effective compared to the active control condition

1. Does POET work better for some individuals than others (i.e., moderation)

Hypothesis 5.1: Individual differences in baseline levels of emotion regulation and mental health problems will moderate treatment outcome.

1. Are there detectable differences in the durability of treatment effects and other distal outcomes between POET and the active control at 1-year, 5-year and 10-year after treatment, and do individual baseline characteristics moderate these effects?

Hypothesis 6.1: Compared to the active control condition, POET is expected to produce greater treatment effects, including reductions in clinical global symptom severity improved emotion regulation ability, reduced maladaptive and enhanced adaptive emotion regulation in the long term, better subsequent academic performance, fewer mental health disorders and self-harm behaviors, and reduced healthcare utilization and consumption of medication for psychiatric symptoms.

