### Adolescent Rated Measures

**Symptoms of depression and anxiety** will be assessed using The Brief Revised Child Anxiety and Depression Scale for Adolescents (RCADS-11)^24^ will be completed by adolescents to assess self-reported symptoms of depression and anxiety. This version consists of 11 items, producing a total score ranging from 0 to 33, with higher scores indicating more severe symptoms.

**Individual differences in emotion regulation** will be measured using a short version (developed for the purpose of this study) of The Process Model of Emotion Regulation Questionnaire - Short (PMERQ).^25^ The scale consists of 30 items, yielding a total score ranging from 30 to 180, with higher scores indicating greater use of emotion regulation strategies. The questionnaire is self-rated by adolescents. Three subscales; Confront Unpleasant Situations (3 items; total score range 6-18), Avoid Unpleasant Situations (3 items; total score range 6-18), and Cognitively Distract (3 items; total score range 6-18) will be administered to adolescents on a weekly basis.

**Difficulties in emotion regulation** will be measured using The Difficulties in Emotion Regulation Scale - 16-item version (DERS-16).^26^ The scale consists of 16 items, yielding a total score ranging from 16 to 80, with higher scores indicating greater difficulties in emotion regulation. The questionnaire is self-rated by adolescents. The DERS-16 is additionally administered to parents to measure their self-reported difficulties in emotion regulation. The Impulse subscale (3 items; total score range 3–15) will be administered weekly during treatment.

**Cognitive reappraisal** will be measured with one subscale of The Emotion Regulation Questionnaire for Children and Adolescents (ERQ-CA).^27^ The cognitive reappraisal subscale consists of 6 items, yielding a total score ranging from 6 to 30, with higher scores indicating greater use of cognitive reappraisal strategies. The questionnaire is self-rated by adolescents.

**Levels of alexithymia** will be measured using The Perth Alexithymia Questionnaire – Short Form (PAQ-S).^28^ The scale consists of 6 items, yielding a total score ranging from 6 to 42, with higher scores indicating greater levels of alexithymia.

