## Statistical methods

### Power analysis

#### Primary outcome

A simulation-based power analysis was performed. Based on the data from the pilot study)^15^, a simpler model without random effects was fitted to estimate the effect of time and the thresholds. Data was then generated using these values, and parameters that were varied, namely sample size, interaction between time and treatment (log-odds), and the variance of the random effect. Sample size took the values of 250, 300, 350, and 400, the interaction effect took the values of 0.59, 0.69, 0.79, and 0.88 (corresponding to ORs of 1.8, 2.0, 2.2, and 2.4), and the variance of the random effect took the values of 1.48 and 2.22 (corresponding to ICC of 0.4 and 0.6). For each combination of parameters, 700 datasets were simulated, and a cumulative link mixed model (CLMM) was fitted to the data. The p-value of the interaction effect was saved for each simulation, and power was calculated as the proportion of p-values less than 0.05. The CLMM model fitted in each iteration included a random intercept for participant, a dummy-coded time variable (before treatment, after treatment), the treatment condition, and the interaction between the time variable and treatment. The results from the power analysis are shown in Figure 2.

We concluded that 350 participants would give us >80% power to detect an interaction between treatment and time with an OR of 2.2. To allow for ~10% attrition, we set N to 388 participants.

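### Hypothesis 3.1 says emotion-regulation change comes before symptom change, but the only named analysis, a parallel-process growth model, does not in its standard form test that order

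*Protocol*

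**What the plan says.** Under *Research questions and hypotheses*, Hypothesis 3.1 makes two claims about the treatment period: "improvement in emotion regulation will temporally precede and mediate reductions in mental health problems during treatment". One claim is order and the other is mediation.

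Under *Secondary objective(s)* the aim is narrower and carries no claim about order: "a mediation analysis to test whether improvements in emotion regulation mediate treatment effects".

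Under *Mediation and moderation analyses* the plan is a single sentence. "Week-to-week changes in facets of emotion regulation will be tested as mediators of POET effects on mental health symptoms", and this is to be done "using parallel process latent growth curve modeling with a competing mediator (SEQ". That sentence gives no time windows, lagged or cross-lagged path, early-mediator and late-outcome split, or test of the reverse direction. Nor does any other part of the protocol.

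The data are dense enough to examine order. Under *Adolescent Rated Measures*, three PMERQ subscales "will be administered to adolescents on a weekly basis". For the DERS-16, "The Impulse subscale (3 items; total score range 3–15) will be administered weekly during treatment". Table 2 also schedules selected ERQ-CA items, the SEQ-C and the RCADS-11 in each of weeks 1 to 6.

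**The concern.** A standard parallel-process growth model summarises each participant's mediator series and symptom series as growth factors (intercept and slope), then regresses the symptom slope on the mediator slope. Both slopes describe the same weeks, so which series moved first within those weeks drops out. The protocol describes the mediators as week-to-week changes, but the named model in its usual form does not retain that ordering.

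An indirect effect in such a model is what one would see if better emotion regulation relieves symptoms. It can also be what one would see if symptom relief improves emotion regulation. Adding self-efficacy as a competitor asks whether emotion regulation is the more specific correlate, and leaves the direction question where it was.

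At stake is the mechanism claim. The protocol's *Background* section cites a shortage of longitudinal evidence on the temporal relation between emotion regulation and psychopathology as part of the case for trials of this kind. As written, the plan collects data that could address that gap but names an analysis that does not.

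**Working it through.** **The plan's own figures.** There is no sample size or power statement for mediation to reproduce. The nearest figures belong to the primary outcome: "350 participants would give us >80% power to detect an interaction between treatment and time with an OR of 2.2", and "To allow for ~10% attrition, we set N to 388 participants". Here 350 / 0.9 = 388.9, against the stated 388, and 388 × 0.9 = 349.2. These agree to within rounding. I use 350 below only as a plausible analysed number.

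**Step 1. Equivalence of the two directions.** Let X be arm, M the emotion-regulation slope and Y the symptom slope.

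- Forward: M = a₀ + aX + e₁; Y = b₀ + c′X + bM + e₂.
- Reverse: Y = d₀ + dX + u₁; M = g₀ + g′X + gY + u₂.

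Each has five regression coefficients and two residual variances. Under normality both are factorisations of one joint density: f(M|X)·f(Y|M,X) = f(M,Y|X) = f(Y|X)·f(M|Y,X). The maximised likelihoods must therefore be equal. Fitted to simulated data in both directions, the largest log-likelihood difference was 3 × 10⁻¹³, which is rounding error. This result needs no assumed effect size. It does require that arm may affect both slopes directly, which is the usual mediation specification.

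**Step 2. What the slope model returns under pure reverse causation (illustration).** All parameters here are assumed; none comes from the protocol. Arm changes the symptom slope by τ = −0.4, the symptom slope has residual variance 1, and M = kY + e with residual variance v. Emotion regulation has no effect on symptoms, so true mediation is 0%.

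- a = kτ
- b = k / (k² + v)
- indirect effect = ab = τ·k² / (k² + v)
- apparent share mediated = k² / (k² + v), which does not depend on τ

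With k = 0.5, a = −0.20, and:

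| v | b | indirect effect | apparent share |
|---|---|---|---|
| 0.25 | 0.5/0.50 = 1.00 | −0.20 | 50% |
| 0.75 | 0.5/1.00 = 0.50 | −0.10 | 25% |
| 2.0 | 0.5/2.25 = 0.22 | −0.044 | 11% |

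If instead k varies with k² + v held at 1, the share is k²: 9%, 25% and 49% for k = 0.3, 0.5 and 0.7.

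**Step 3. Simulation of trials with a one-week lead.** There were 1,000 trials per scenario, each with 350 participants and six weekly waves. The assumptions for the leading process were an arm effect of −0.15 per week, person-level rate SD 0.15 and weekly noise SD 0.2. The follower moved by 0.7 of the leader's previous weekly change, and measurement error SD was 0.5. Least-squares slopes per participant stood in for latent slopes, and the indirect effect was judged by a Sobel test.

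| True order | Indirect effect through emotion regulation significant | Emotion-regulation change with next-week symptom change (mean r) | Reverse (mean r) |
|---|---|---|---|
| Emotion regulation leads | 100% | 0.084 | 0.034 |
| Symptoms lead | 99.6% | 0.034 | 0.085 |

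The slope-based test gives almost the same answer in both worlds. The lagged comparison on the same data separates them. The weaker direction is not zero, because the simulated participants have persistent trends and treatment effects on those trends. Only the contrast between directions is informative.

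**The case against.** The strongest reply is that the plan for this aim is one sentence, and that time windows and path structure are details a protocol may leave to an analysis plan that is not at hand. A phased variant (early mediator slope, later symptom slope) or one with lagged paths could address order, and the reference to week-to-week changes is compatible with such an intent. This stands as a limit. A reader might infer that the plan cannot test order at all, or that it rules out any lag. The protocol does not support that, because it fixes no windows. The criticism applies to the named model in its standard form. The mismatch remains because the protocol commits to a hypothesis about order and to a named model, and states nothing that links them.

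Four further limits also stand.

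- A reader might infer that the weekly data go unused. They do not: they are what the growth curves are fitted to. What has no stated use is their ordering.
- A reader might take a single value such as 25% as an estimate for this trial. It is one row of an illustration, and the result moves from 11% to 50% with an assumed variance. The 99.6% likewise rests on assumed parameters and simplified slopes.
- A reader might infer that the investigators will report any significant indirect effect as proof of mechanism. The protocol contains no such reporting rule.
- Growth-model mediation is an ordinary choice for the aim as worded under *Secondary objective(s)*, which makes no claim about order. There is no need to displace it with one particular lagged model. The documents give no basis for a one-week lag, and a random-intercept cross-lagged model needs extra handling when treatment produces trends.

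**Conclusion.** The concern holds in limited form. Hypothesis 3.1 claims that emotion-regulation improvement comes first, and the only analysis named for it does not, in its standard form, test that claim. The two directions are statistically equivalent at slope level, and the competing mediator does not change this.

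The equivalence rests only on the standard specification. The sizes (11% to 50% spurious mediation; near-identical significance rates whichever process leads) rest on assumed parameters and show what can happen, not what will happen in this trial.

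Only the precedence part of one hypothesis, under an additional secondary aim, is affected. The growth model can still estimate arm effects on both slopes and their association. The primary outcome, its sample size and its inference are untouched. The change is worth making because it is cheap and bears on a question the protocol itself raises.

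**What to change.** Keep the parallel-process growth model for the mediation aim. Add to *Mediation and moderation analyses* a pre-specified lagged analysis of the weekly data, for example a latent change-score or cross-lagged model that allows for treatment-related trends. It should estimate both the path from emotion regulation at week t to RCADS-11 at week t+1 and the reverse path. State that any conclusion about precedence will rest on comparing the two. SEQ-C can be carried into this model as the competing mediator.

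If that is not wanted, remove *temporally precede* from Hypothesis 3.1 and state that the direction of the slope-to-slope path is assumed. This is a wording change only.

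The first option needs no new data, since all series are already scheduled in weeks 1 to 6. It costs moderate extra modelling. It also carries an assumed one-week lag, which should be declared as such, and it leaves unmeasured confounding between mediator and symptoms in place. Either option should be fixed before the mediation data are analysed, so that the model is not chosen on its results.

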### Long-term and distal outcomes data

Additional analyses of primary and secondary outcomes at 1-year and 5-year follow-up will assess whether treatment effects are sustained over the long term, using the same statistical analysis method applied at the primary endpoint. Data on distal outcomes will be obtained from Swedish national registries. This data will vary in type and distribution such as continuous (e.g., grade point average), binary (e.g., eligibility for higher education), count (e.g., number of health care contacts), and time-to-event (e.g., suicide), appropriate regression models will be fitted accordingly.

# Methods: Monitoring

## Trial monitoring

We will use internal monitoring as part of the quality control in this study. The monitoring process ensures that the rights, safety, and well-being of research participants are protected and that the collected data are accurate. This is done by reviewing compliance with the study protocol, applicable laws and regulations, and by ensuring that study data are recorded in a correct and traceable manner.

## Quality Control and Quality Assurance

Although this trial is not a pharmaceutical trial, it will adhere to the main Good Clinical Practice principles. The trial will be performed in compliance with this clinical trial protocol and current national regulations governing this clinical trial. This is to ensure the safety and integrity of the trial subjects as well as the quality of the data collected. In the event of harm resulting from participation in the study, participants are covered by applicable national patient injury insurance, in accordance with local regulations.

# Ethics

The study has obtained ethical approval from the Swedish Ethical Review Authority (approval no. 2023-03652-0) and was pre-registered before recruitment commenced at ClinicalTrials.gov (ID: NCT06067165). Eventual protocol amendments will be reported to the Swedish Ethical Review Authority and registered at ClinicalTrials.gov. All participants will provide informed consent. Participants aged 15 years or older and parents will provide written consent. Younger participants will provide verbal consent with parental written consent.

## Benefit-risk evaluation

No immediate negative effects are expected as a possible consequence of the treatment programs or assessment procedures. Extensive follow-up period may be perceived as burdensome, but it is considered a necessary part of the evaluation of the treatments. The risk of discomfort during the assessment process is judged to be less serious than the risk of including unsuitable participants in the treatments. The risks and burdens identified in relation to study participation are few and can largely be mitigated through clear information and continuous monitoring of participants’ well-being. On the other hand, the potential benefits of the project are substantial. This study has the potential to contribute valuable knowledge on how scalable, structured, and accessible treatments can be implemented within routine healthcare. The study also offers direct benefits to participants by providing prompt access to free psychological treatment, including weekly therapist support, with the potential for symptom reduction and decreased suffering.

## Measures to minimize risks for participants

Acute problems (e.g., deterioration of mental health problems) may occur. To manage this, weekly contact with a therapist is included as part of the treatment (regardless of treatment condition), and families also have the opportunity to reach out on their own initiative. Families experiencing acute problems will be actively supported in obtaining appropriate care. Therapists will also review participants’ self-assessments weekly to identify any deterioration in well-being that has not been communicated during treatment. Participants who continue to need psychological treatment after the 6-week intervention will be offered referral to appropriate services within regular care in their region.

Being excluded from the study may be perceived as negative. Therefore, clear information about the inclusion and exclusion criteria is available on the project’s website. In cases of exclusion, participants will receive personal feedback and, when appropriate, referral to adequate care.

Clear, age-appropriate information about the project is provided to all potential participants. Both adolescents and parents/guardians are informed that they may withdraw from the study at any time, and they receive information about confidentiality and data handling.

# Handling of Adverse Events

## Definition: Adverse Event (AE)

Adverse Event (AE): Any untoward medical occurrence in a subject to whom a medicinal product is administered and which does not necessarily have a causal relationship with this treatment.

## Definition: Serious Adverse Event (SAE)

Serious Adverse Event (SAE): Any untoward medical occurrence that at any dose requires inpatient hospitalization or prolongation of existing hospitalization, results in persistent or significant disability or incapacity, is life-threatening, or results in death.

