## Secondary endpoint

Secondary endpoints are:

- 3 months after treatment.
- 1 years after treatment.
- 5 years after treatment.
- Distal outcomes will be examined after the participant’s 18th birthday using data from Swedish national registries retrieved 1 to 10 years after treatment completion, depending on age at study inclusion.
- Weekly during treatment.

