### Exclusion criteria:

- Severe mental illness requiring specialized care or low global functioning corresponding to a Children’s Global Assessment Scale (CGAS) score of less than 41 on a scale of 1 to 100 (higher scores indicating better functioning).
- Acute suicidality, (ongoing suicide plans or recent suicide attempt).
- Ongoing psychological treatment.
- Changes in psychopharmacological medication during the past 2 months.
- Insufficient Swedish comprehension.
- Life circumstances that could prevent treatment participation acute suicidality, (ongoing suicide plans or recent suicide attempt).

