### Screening and inclusion

Subject eligibility (that subjects fulfil all inclusion criteria and do not meet any exclusion criteria) is established before randomization. Participants can be referred by other treatment provider or make a self-referral via the self-assessment tool and website called BASS (centrally administered by the sponsor Karolinska Institutet). When potential participants have been referred to the study or have made a self-referral, a therapist (psychologist, psychotherapist or clinical psychology M.Sc. student under supervision) will contact the guardian for an initial telephone screening to evaluate whether the youth fills inclusion and not exclusion criteria. The therapist will explain the study procedure and any questions regarding the procedure will be answered. This initial screening is estimated to take about 15 minutes. If still interested, the potential participant and guardian is invited to a digital video-call clinical assessment. Before this assessment, the guardian and adolescent receive login information to the self- assessment tool BASS, where the research person information, self- assessment measures and informed consent registration are available. Guardians and adolescents answer self-assessment measures and informed consent is collected. The part of the study concerning distal outcomes is optional. If participants choose not to consent to the retrieval of registry data, this will not affect their participation in the study or the treatment they receive. Potential participants and parents completed an assessment interview over video link, including a semi structured interview,^11^ and clinician-assessed forms. Any questions that the participant or guardians have regarding the procedure is answered. Individuals who meet the inclusion criteria and no exclusion criteria are offered participation in the study. If needed, excluded participants receive recommendations for other treatment.

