**Non-suicidal self-injury (NSSI)** during the past month will be assessed by a clinician prior to randomization, using a single clinician-administered item from the Mini International Neuropsychiatric Interview for Children and Adolescent*s* (MINI-KID).^11^

**Self-harm** will be measured using Deliberate Self-Harm Inventory - Youth Version DSHI-Y).^29^ DSHI-Y measures the occurrence, methods, and frequency of deliberate self-harm. The scale consists of 6 items, with higher scores indicating more frequent engagement in self-harm behaviors.

**Positive and negative affect** will be measured using the *Positive and Negative Affect Schedule for Children* (PANAS).^30^ The scale includes two subscales, each with a total score ranging from 5 to 25, where higher scores indicate greater levels of the corresponding affect (positive or negative).

**Self-efficacy** will be measured using the Social Self-Efficacy subscale of Self-Efficacy Questionnaire for Children (SEQ-C).^31^ The Social Self-Efficacy subscale consists of 8 items, yielding a total score ranging from 8 to 40, with higher scores indicating greater perceived social self-efficacy.

**High-risk and problematic behaviors** will be measured using *Borderline Symptoms List Supplement* (BSL-23).^32^ BSL- 23 assess engagement in high-risk and maladaptive behaviors. The scale consists of 10 items, yielding a total score ranging from 0 to 40, with higher scores indicating greater frequency of such behaviors. This version is study-specific and adapted for use in primary care.

**Beliefs about emotions** will be measured using Emotion Beliefs Questionnaire (EBQ).^33^ The scale consists of 16 items, yielding a total score ranging from 16 to 112, with higher scores indicating more maladaptive beliefs about emotions.

**Health-related quality of life** will be measured using the Child Health Utility 9D (CHU-9D).^34^ The CHU-9D consists of 9 items assessing different aspects of health-related quality of life, with a total score ranging from 9 to 45. Higher scores indicate poorer quality of life. CHU-9D has a validated algorithm for calculating QALY in children and adolescents.

**Adverse events:** Participants are asked to report and rate the discomfort of the eventual adverse events caused by their participation in the treatment. These questions will be administered to all adolescents at immediately after treatment.

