# Table 1. Relevant registers and the types of data to be collected for analyses of distal outcomes

| **Register** | **Data of interest** |
| --- | --- |
| National Patient Register | Diagnosis, healthcare utilization, type of care, and suicide attempts |
| VAL Database | Diagnosis, healthcare utilization, type of care, and suicide attempts |
| Prescribed Drug Register | Prescription and consumption of medication for psychiatric symptoms |
| LISA (Longitudinal Integration Database for Health Insurance and Labour Market Studies) | Employment status, sick leave, and highest educational level |
| Swedish National Agency for Education: Quality Declaration, Compulsory School (final grades) | Grades and eligibility |
| Swedish National Agency for Education: Quality Declaration, Upper Secondary School (grade records) | Grades and eligibility |

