# Table 2. Information on the time points for completion and responders of measurements related to all hypotheses

|  | TRIAL PERIOD | | | | | | | | | | | | |
| --- | --- | --- | --- | --- | --- | --- | --- | --- | --- | --- | --- | --- | --- |
|  | Enrolment | Randomization | Post-randomization | | | | | | | | | | |
| Assessment point | Baseline | | 1w | 2w | 3w | 4w | 5w | 6w | POST | 3M | 12M | | 60M |
| **ENROLMENT** |  | |  |  |  |  |  |  |  |  |  | |  |
| Eligibility screen | X | |  |  |  |  |  |  |  |  |  | |  |
| Informed consent | X | |  |  |  |  |  |  |  |  |  | |  |
| Randomization | X | |  |  |  |  |  |  |  |  |  | |  |
| **TREATMENT**  POET  Supportive treatment |  | |  | | | | | |  | | | | |
| **ASSESSMENTS** |  | |  |  |  |  |  |  |  |  | |  |  |
| ***Clinician rated*** |  | |  |  |  |  |  |  |  |  | |  |  |
| MINI-KID | X | |  |  |  |  |  |  |  |  | |  |  |
| CGI-S | X | |  |  |  |  |  |  | X | X | | X | X |
| CGI-I |  | |  |  |  |  |  |  | X | X | | X | X |
| C-GAS | X | |  |  |  |  |  |  | X | X | | X | X |
| WSAS | X | |  |  |  |  |  |  | X | X | | X | X |
| RCADS-47 | X | |  |  |  |  |  |  | X | X | | X | X |
| CEQ | X | |  |  | X |  |  |  |  |  | |  |  |
| PIAS |  | |  |  | X |  |  |  | X |  | |  |  |
| ***Adolescent rated*** |  | |  |  |  |  |  |  |  |  | |  |  |
| RCADS-11 | X | | X | X | X | X | X | X | X | X | | X | X |
| PMERQ-short | X | |  |  |  |  |  |  | X | X | | X | X |
| Selected items from PMERQ-short |  | | X | X | X | X | X | X |  |  | |  |  |
| DERS-16 | X | |  |  |  |  |  |  | X | X | | X | X |
| Selected items from DERS-16 |  | | X | X | X | X | X | X |  |  | |  |  |
| ERQ-CA | X | |  |  |  |  |  |  | X | X | | X | X |
| Selected items from ERQ-CA |  | | X | X | X | X | X | X |  |  | |  |  |
| PAQ-S | X | |  |  |  |  |  |  |  | X | | X | X |
| DSHI-Y |  | |  |  |  |  |  |  | X | X | | X | X |
| PANAS | X | | X | X | X | X | X | X | X | X | | X | X |
| SEQ-C | X | | X | X | X | X | X | X | X | X | | X | X |
| BSL-23 | X | |  |  |  |  |  |  | X | X | | X | X |
| EBQ | X | |  |  |  |  |  |  | X | X | | X | X |
| CHU-9D | X | |  |  |  |  |  |  | X | X | | X | X |
| CSQ |  | |  |  |  |  |  |  | X |  | |  |  |
| Study specific questionnaire on Adverse events |  | |  |  |  |  |  |  | X |  | |  |  |
| CEQ | X | |  |  |  |  |  |  |  |  | |  |  |
| One selected item from CEQ |  | | X | X | X | X | X | X |  |  | |  |  |
| Single-item assessment of suicidal ideation and plans | X | | X | X | X | X | X | X | X | X | | X | X |

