## Assessment of Adverse Events (AE)

Participants are asked to report adverse events during treatment period and rate the discomfort of the eventual adverse events caused by their participation in the treatment. These questions will be administered to adolescents immediately after treatment.

During treatment, AE and SAR are registered by a clinician. All AE that occurs during the trial and which are observed by a clinician or reported by the subject will be registered regardless of whether they are assessed as related to the treatment of not. Assessment of causal relationship, severity (mild, moderate, severe), and whether the AE is considered to be an SAE will be made by the project investigator. For each AE/SAE, a description of the event is recorded, start date for the AE/SAE, planned actions, actions taken, causal relationship, and whether it is an AE or SAE. Serious Adverse Events (SAE) are reported to the sponsor within 24 hours of the investigator being informed of the SAE.

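### A suicide attempt without admission, and not judged life-threatening or disabling, is a non-serious adverse event with no deadline for reaching the sponsor

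*Protocol*

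**What the plan says.** Under *Definition: Serious Adverse Event (SAE)*, an event is serious if it "requires inpatient hospitalization or prolongation of existing hospitalization, results in persistent or significant disability or incapacity, is life-threatening, or results in death". No further criterion follows.

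Under *Assessment of Adverse Events (AE)*, all adverse events are registered whether or not they are related to treatment. The project investigator decides causality, severity and seriousness. One deadline is set: "Serious Adverse Events (SAE) are reported to the sponsor within 24 hours of the investigator being informed of the SAE".

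Suicide attempts are named in two other places. The exclusion criteria list "Acute suicidality, (ongoing suicide plans or recent suicide attempt". Table 1 lists "Diagnosis, healthcare utilization, type of care, and suicide attempts" as data from two registers. The adverse event sections do not mention attempts.

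**The concern.** The trial treats adolescents with mental health problems, and a suicide attempt is among the safety events most specific to them. Under the definition as written, the attempt itself does not count. It becomes serious only through its consequence: admission, danger to life, disability or death. For the remaining attempts, classification depends on local admission practice, in a trial that recruits nationally and randomizes within Regions, and on how life-threatening is judged, a term the protocol leaves undefined.

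Two things are at stake. The sponsor has no set time within which to learn of such an attempt in a minor. The SAE category, when reported by arm, would also leave it out. The definition looks like drug-trial text that was not adapted: the adverse event definition refers to administration of a medicinal product, and the SAE definition refers to dose.

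**Working it through.** No formula applies and the protocol states no figure to reproduce. The check applies the definition to a case and then looks for any other rule that would catch it.

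**Step 1: apply the criteria.** Take a hypothetical participant who makes an attempt with intent to die, is seen and sent home, and has no lasting harm.

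| SAE criterion | Met? |
|---|---|
| Admission, or a longer existing stay | No |
| Lasting or significant disability or incapacity | No |
| Life-threatening | No, if not so judged |
| Death | No |

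None of the four is met, so the event is a non-serious adverse event.

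**Step 2: look for a deadline.** The adverse event sections contain one timed report to the sponsor, the 24-hour report, and it covers SAEs only. The other response time checked, two working days under *Therapist contact*, concerns therapist feedback to families and is not a safety report.

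**Step 3: look for another route.**

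- *Assessment of expected AE*: thoughts about death or suicide are on the expected list and attempts are not, so an attempt is unexpected by default. No report follows from being unexpected.
- *Assessment of intensity*: an event that puts the participant's health at risk can be graded severe. No report follows from the grade.
- *Measures to minimize risks for participants*: weekly therapist contact, weekly review of self-assessments and help in obtaining care protect the adolescent in both arms. They do not inform the sponsor.
- Table 2, "Single-item assessment of suicidal ideation and plans": 1 baseline + 6 weekly + 4 later (post-treatment, 3, 12 and 60 months) = 11 time points. The item covers ideation and plans, not attempts.
- Table 2, DSHI-Y: 4 time points (post-treatment, 3, 12 and 60 months), 0 of the 6 treatment weeks. According to *Adolescent Rated Measures*, "DSHI-Y measures the occurrence, methods, and frequency of deliberate self-harm". It is not described as identifying suicide attempts.
- Table 1 registers: these name attempts, but "The part of the study concerning distal outcomes is optional", and outcomes are examined "using data from Swedish national registries retrieved 1 to 10 years after treatment completion". They serve long-term outcome analysis, not safety reporting.

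**Result.** No other section gives the attempt in Step 1 SAE status or a reporting time.

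**The case against.** The strongest reply is that nothing is contradicted. The definition and the reporting rule agree with each other, a named person decides seriousness, and that person may judge an attempt life-threatening. The exclusion of recent attempts is an eligibility rule and implies no seriousness class. The subset is narrow, because acute suicidality is excluded at entry and admitted, life-threatening, disabling or fatal attempts are already SAEs. The event stays visible: it is registered with a description, start date, actions and causality, is unexpected by default, and can be graded severe. There is no interim analysis, monitoring is internal, and no stated action follows when the sponsor receives an SAE, so no change in any participant's care is shown. The remedy also brings in new judgements, about intent to die and medical importance.

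Much of this stands. The entry criterion is only context: it shows that the protocol elsewhere treats an attempt as important without asking about admission. The questionnaire and register counts show that no scheduled source fills the gap; they do not measure its size. The subset may be empty.

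The conclusion survives. Registration gives neither SAE status nor a deadline, and no rule obliges the investigator to call an attempt life-threatening. If that is the intention, it costs little to write it down. Judging intent is unavoidable, but it concerns the act itself and does not vary with whether a bed was used.

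**Conclusion.** The point holds. Following the protocol exactly, a suicide attempt that is not admitted and not judged life-threatening or disabling is a non-serious adverse event with no time limit for reaching the sponsor; listing it would bring the existing 24 hours into force. This is a safety-reporting weakness that should be corrected, not an error in the efficacy analysis: the primary estimate, power and alpha do not change. The conclusion rests on the text alone. No attempt rate or admission rate is given, so the number of affected events is unknown and could be zero.

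**What to change.** Add to the SAE definition that the following are serious:

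- any suicide attempt, meaning a self-injurious act with at least some intent to die, as distinct from non-suicidal self-injury, whether or not the adolescent is admitted;
- any other event the investigator judges medically important.

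Where intent is unclear, the investigator decides and records the reason. The existing 24-hour report then applies from the amendment onward. The amendment should also say how long that duty lasts, since the protocol refers to registration both during treatment and during the trial, and follow-up runs for years.

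Reclassify adverse events already recorded by the same rule in both arms. Someone masked to allocation should do this from descriptions with treatment content removed, because therapists and the project manager know the allocation. For past events only the label changes; the main fix does not depend on this step. Removing the medicinal-product and dose wording is an editorial clean-up.

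The cost is an amendment reported to the ethics authority and the trial registry as the *Ethics* section provides, one masked review of recorded descriptions, and possibly some extra 24-hour reports whose number cannot be estimated from the protocol. Separating attempts from the self-injury and self-harm the trial also measures will need some investigator judgement.
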